# Radiofrequency ablation via catheter and transpapillary access in patients with cholangiocarcinoma (ACTICCA-2 trial) – a multicenter, randomized, controlled, open-label investigator-initiated trial

**DOI:** 10.1186/s12885-024-12693-w

**Published:** 2024-08-01

**Keywords:** Cholangiocarcinoma, CCA, Biliary tract cancer, Klatskin tumor, Biliary ablation, Bile duct stenting, Radiofrequency ablation, Palliative chemotherapy, Immunotherapy

## Abstract

**Background:**

Despite the recent advances in cancer treatment, the therapeutic options for patients with biliary tract cancer are still very limited and the prognosis very poor. More than 50% of newly diagnosed patients with biliary tract cancer are not amenable to curative surgical treatment and thus treated with palliative systemic treatment. Malignant bile duct obstructions in patients with perihilar and/or ductal cholangiocarcinoma (CCA) represents one of the most important challenges in the management of these patients, owning to the risk represented by developing life-threatening cholangitis which, in turn, limits the use of systemic treatment. For this reason, endoscopic stenting and/or bile duct decompression is the mainstay of treatment of these patients. Data on efficacy and safety of adding radiofrequency ablation (RFA) to biliary stenting is not conclusive. The aim of this multicenter, randomized trial is to evaluate the effect of intraductal RFA prior to bile duct stenting in patients with unresectable perihilar or ductal CCA undergoing palliative systemic therapy.

**Methods/Design:**

ACTICCA-2 is a multicenter, randomized, controlled, open-label, investigator-initiated trial. 120 patients with perihilar or ductal CCA with indication for biliary stenting and systemic therapy will be randomized 1:1 to receive either RFA plus bile duct stenting (interventional arm) or bile duct stenting alone (control arm). Patients will be stratified by trial site and tumor location (perihilar vs. ductal). Both arms receive palliative systemic treatment according to the local standard of care determined by a multidisciplinary tumorboard. The primary endpoint is time to first biliary event, which is determined by an increase of bilirubin to > 5 mg/dl and/or the occurrence of cholangitis leading to premature stent replacement and/or disruption of chemotherapy. Secondary endpoints include overall survival, safety according to NCI CTCAE v5, quality of life assessed by questionnaires (EORTC QLQ-C30 and QLQ-BIL21), clinical event rate at 6 months after RFA and total days of over-night stays in hospital. Follow-up for the primary endpoint will be 6 months, while survival assessment will be continued until end of study (maximum follow-up 30 month). All patients who are randomized and who underwent endoscopic stenting will be used for the primary endpoint analysis which will be conducted using a cause-specific Cox proportional hazards model with a frailty for trial site and fixed effects for the treatment group, tumor location, and stent material.

**Discussion:**

ACTICCA-2 is a multicenter, randomized, controlled trial to assess efficacy and safety of adding biliary RFA to bile duct stenting in patients with CCA receiving palliative systemic treatment.

**Trial registration:**

The study is registered with ClinicalTrials.gov (NCT06175845) and approved by the local ethics committee in Hamburg, Germany (2024-101232-BO-ff). This manuscript reflects protocol version 1 as of January 9th, 2024.

**Graphical Abstract:**

[figure not shown]

**Supplementary Information:**

The online version contains supplementary material available at 10.1186/s12885-024-12693-w.

## Background

### Epidemiology of biliary tract cancer and medical problem

Despite new therapeutic options to treat malignancies, mortality for liver cancer, and particularly for biliary tract cancer, is rising and the prognosis is very poor [1]. At the same time, therapeutic options remain very limited, particularly for patients with biliary tract cancer not amenable to curative surgical resection. [1, 2]. The age-standardized incidence rate of cholangiocarcinoma (CCA) in western countries is 0.3–3.5 cases per 100 000. However, in Asian countries the incidence is up to 40 times higher, reaching 85 cases per 100 000 in Thailand. Especially the incidence of intrahepatic CCA has been steadily increasing in most Western countries, and less than 50% of these newly diagnosed patients are amenable to curative surgical therapy [2].

Regarding patients with unresectable CCA, systemic therapy unequivocally represents the standard of care [2]. However, patients with perihilar and/or ductal CCA are in danger of developing life-threatening cholangitis due to malignant bile duct obstruction and often require prophylactic stenting and/or bile duct decompression before and during the administration of palliative chemotherapy [1, 2]. In a large proportion of these patients (approximately 30% in 3 months), stent dysfunction and episodes of cholangitis occur resulting in a delay of systemic therapy. Therefore, additional intraductal therapies, specifically photodynamic therapy (PDT) [3] and endobiliary radiofrequency ablation (RFA) [4], have been investigated for the management of malignant biliary obstructions and to improve stent patency. Despite a convincing mechanistic rationale for these intraductal interventions and a huge medical need, evidence comparing RFA plus stenting and stenting alone is scarce and/or conflicting, particularly regarding effects in the setting of palliative chemotherapy [5–9].

### Treatment modalities for unresectable biliary tract cancer

Based on an investigator-initiated trial (IIT) by Valle et al., including more than 750 patients, palliative chemotherapy with gemcitabine and cisplatin has been the standard of care (SOC) for patients with unresectable biliary tract cancer [10–12].

Recently, the phase III clinical trial TOPAZ-1 evaluating the PD-L1 antibody durvalumab in combination with gemcitabine and cisplatin against gemcitabine and cisplatin alone in patients with unresectable biliary tract cancer has met its primary endpoint with increased overall survival (OS) for the triple combination (12.8 vs. 11.5 months, hazard ratio of 0.8 (95% confidence interval [CI]: 0.66, 0.97) [13]. In contrast, data regarding the efficacy and safety of adding PDT or RFA to biliary stenting in patients with biliary obstruction who are in need for systemic therapy, is limited and conflicting.

A recent meta-analysis from 2021 assessed the role of PDT, RFA, and biliary stenting alone in the palliative treatment of unresectable extrahepatic CCA [14]. A total of 1149 patients underwent treatment with PDT (33 studies), 545 with RFA (22 studies), and 452 patients with stent-only strategy. The pooled median survival with PDT, RFA, and stent-only groups was 11.9 (95% CI: 10.7–13.1) months, 8.1 (95% CI: 6.4–9.9) months, and 6.7 (95% CI: 4.9–8.4) months, respectively. However, the subgroup of endoscopic RFA (235 patients, excluding percutaneous ablation) yielded a median OS of 12 (95% CI: 9.8–14.3) months, similar to PDT. The study reported a pooled time of stent patency for PDT, RFA, and stent-only groups of 6.1 (95% CI: 4.2–8) months, 5.5 (95% CI: 4.2–6.7) months, and 4.7 (95% CI: 2.6–6.7) months, respectively. Regarding adverse events, the pooled rates of cholangitis and liver abscess were highest among patients undergoing PDT compared to RFA and stent-only groups (cholangitis; 23.4%, 9.5%, 15.5%; liver abscess: 4.9%, 2.6%, 2.1%), whereas the pooled rates of hemobilia were comparable between PDT, RFA, and stent-only (5.4%, 4.3%, 3.2%). However, it is important to emphasize that large randomized studies directly comparing these procedures are lacking [15].

Early studies investigating the effects of RFA reported relatively high rates of complications and adverse events, which was likely due to the relatively new procedure. In a retrospective study from 2014, 19 endoscopic ablations were performed in 12 patients with unresectable malignant hilar bile duct obstruction [16]. Four of the 12 patients also received chemotherapy. The median OS from the time of the first RFA was 6.4 months. In this cohort, biliary bleeding was observed in 3 cases and severe cholangitis in another 3 patients. Along this line, a collaborative registry trial from the U.S. also reported a high rate of adverse events (10%) in 69 patients, of whom 78% also received chemotherapy, again with mixed aetiologies of malignant biliary obstructions undergoing intraductal RFA [17]. A small study in the U.S. compared OS rates in patients receiving RFA (*n* = 16) or PDT (*n* = 32) and did not report a statistically significant difference (9.6 months for RFA versus 7.5 months for PDT, *p* = 0.799) for these interventions [18]. In this study however, patients who underwent RFA (compared to PDT) had a lower mean number of plastic stents placed per month (0.45 vs. 1.10, *p* = 0.001), but had more episodes of stent occlusion (0.06 vs. 0.02, *p* = 0.008) and cholangitis (0.13 vs. 0.05, *p* = 0.008) per month. In addition, the complication rate in this study (stent occlusion and/or cholangitis requiring premature stent replacement) interfering with the administration of palliative chemotherapy was 7–19% per month or 20–40% in 3 months in patients receiving additional transductal interventions (RFA or PDT). Finally, a recent study compared adverse events and short-term effects of RFA (*n* = 14) vs. PDT (*n* = 20) in perihilar CCA [19]. In the PDT group, a significantly higher number of premature stent replacements (< 3 months) after the first intervention was noticed in comparison with the RFA group (65% vs. 29%, *p* < 0.01). Between the first and fifth stent replacement, post-interventional adverse events tended to occur more frequently in patients with PDT than with RFA (40% vs. 21%, *p* = 0.277).

More recently, three randomized controlled trials were reported. Most recently, a multicenter study including patients with CCA and pancreatic cancer with malignant biliary obstruction by Jarosova et al. (2023) compared endoluminal RFA plus stenting and stenting alone. In this study, OS did not differ significantly between the RFA group and the control group among patients with CCA (10.5 vs. 10.6 months, *n* = 85, *p* = 0.58), and no benefit was seen in the RFA group with regards to stent patency (40% vs. 36% at 12 months), quality of life, and adverse event rate [6]. The study was therefore prematurely terminated due to futility. Noteworthy, the RFA group contained more patients with distal CCA (18% vs. 10%), which is considered to have a worse prognosis compared to hilar CCA, and less patients with concomitant (9% vs. 20%) or adjuvant (20% vs. 37%) anti-cancer therapy rendering a potential bias in the survival analysis. In contrast, studies by Gao et al. and Yang et al. reported improved OS when comparing RFA plus stenting vs. stenting alone. Gao et al. performed a multicenter randomized trial, including 47 patients with hilar CCA and 100 patients with distal CCA, and reported an OS of 13.3 months in the RFA group vs. 9.2 months in the control group (hazard ratio 0.546, *p* < 0.001). However, no significant differences were found regarding jaundice control or stent patency duration between the groups [7]. Noteworthy, this study was limited to patients who were not eligible for systemic therapy, thus reflecting a different patient population compared to our study design. In line with this, Yang et al. performed a single-center randomized trial in patients with perihilar or distal CCA (*n* = 65) and reported an OS of 13.2 vs. 8.3 months (*p* < 0.001) for RFA plus stenting vs. stenting alone [9]. However, the latter trial did not include data on systemic chemotherapy as SOC in these patients. In conclusion, evidence is scarce and inconsistent and thus comparing RFA plus stenting vs. stenting alone in the context of systemic chemotherapy in patients with unresectable CCA is strongly required.

### Study rationale

As discussed before, conflicting data has been reported for patients receiving intraductal therapy (RFA or PDT) for malignant bile duct obstructions compared to stenting alone. RFA seems to be equally effective regarding OS and stent patency compared to PDT, but with a lower number of complications [14, 20]. Taken together, it is reasonable to assume that the improved OS in patients treated with endoscopic RFA compared to stent alone is likely due to the longer stent patency and fewer stent replacements which prevent life-threatening biliary complications and interruptions of systemic chemotherapy. However, these findings are mainly derived from retrospective studies and early reports on complications (hemobilia, cholangitis, stent obstruction) make it difficult to judge, whether intraductal RFA in addition to stenting of malignant biliary obstructions is beneficial in patients with unresectable perihilar and/or ductal CCA, particularly in the setting of palliative chemotherapy as SOC [5, 15]. Unfortunately, standard systemic therapy was not included in any of the recent randomized trials [6, 9, 21].

Data on prognostic factors for CCA are rare. Within the current trial, tumor tissue (if available), bile fluid, plasma, and buffy coat will be collected with the clinical data. An allocation database will be established gathering the data of the available patient samples at each study site to enable translational research.

### Study objective

The primary objective of this study is to evaluate the efficacy of intraductal RFA prior to stent placement compared to stent placement alone in patients with perihilar or ductal CCA who receive systemic treatment. The secondary objectives are OS, safety, quality of life (QoL), clinical event rate, and days of overnight hospital stays.

### Methods/Design

The ACTICCA-2 study is a multicenter, prospective, randomized, open-label trial designed to assess the clinical performance of intraductal RFA plus biliary stenting in comparison to stenting alone both in combination with palliative systemic treatment in patients with CCA. A total of 120 patients will be assigned to the trial and randomized 1:1 to receive either RFA plus biliary stenting or stenting alone (*n* = 60 per arm). Patients will be followed up for a minimum of 6 months. The total study duration will be 30 months. Patient recruitment will be initiated in August 2024.

### Patient selection and randomization

Patients will be enrolled into the trial according to the eligibility criteria (Table 1). Inclusion and exclusion criteria are based on the main selection criteria for patients with unresectable perihilar and/or ductal CCA who are recommended to receive bile duct stenting and palliative systemic therapy by current guidelines [2]. In detail, these criteria reflect the patient’s clinical status including potential safety concerns regarding the endoscopic intervention and administration of systemic chemotherapy. Performance status 0–1 according to the Eastern Cooperative Oncology Group (ECOG) is a well-established cut-off for the eligibility of patients to receive systemic therapy and invasive procedures, such as endoscopic retrograde cholangiopancreatography (ERCP). Patients will be excluded if prior RFA and/or multiple stenting for CCA has been performed during the past 3 months to rule out competing effects on the outcome analysis (first stent replacement or placement of the first stent for tumor-related bile duct obstruction within 3 months prior to study inclusion is allowed). Patients with concomitant diseases or malignancies with limited prognosis or high likelihood of study discontinuation (e.g. severe or uncontrolled cardiovascular disease, such as congestive heart failure New York Heart Association (NYHA) III or IV, unstable angina pectoris, myocardial infarction within ≤ 3 months, and/or significant arrhythmias) will be excluded. This is in line with clinical eligibility criteria for the administration of bile duct stenting and subsequent administration of systemic therapy. Taken together and considering a relatively large sample size and a multicenter study design, the study population is representative, and results are generalizable to the target population of interest.

**Table 1 Tab1:** Eligibility criteria for the ACTICCA-2 enrollment phase

Unresectable perihilar and/or ductal CCA with indication for bile duct stenting
Signed written informed consent
ECOG performance status 0–1
Age ≥ 18 years
Eligibility for palliative systemic therapy based on clinical and laboratory parameters (except hyperbilirubinemia) as determined by the local MDT
No prior RFA for CCA
No repeated bile duct stenting for > 3 months (trial inclusion is possible upon first stent replacement or initial stent placement)
No concomitant disease or malignancy interfering with the study procedure or efficacy outcome measures, particularly no severe or uncontrolled cardiovascular disease (congestive heart failure NYHA III or IV, unstable angina pectoris, myocardial infarction within ≤ 3 months, significant arrhythmias) and no psychiatric disorders precluding understanding of information of trial related topics and giving informed consent

*CCA*: cholangiocarcinoma, *ECOG*: Eastern Cooperative Oncology Group, *RFA*: radio frequency ablation, *NYHA*: New York Heart Association Functional Classification, *MDT*: multidisciplinary team

Randomization to study treatment should occur within three weeks after eligibility criteria have been met. Study subjects will be randomized by the electronic CRF to arm A (intervention group) or B (control group) in 1:1 ratio, stratified by trial site and tumor location (perihilar vs. ductal). The procedure itself (i.e., endoscopic stenting with or without RFA) and randomization are on the same day.

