#### Screening

Within 3 weeks prior to randomization/start of first treatment (i.e. stenting with or without RFA) the following will be assessed/obtained:

Signed written informed consent.Medical history including previous cancer history, cancer treatment, concomitant diseases, current medication, prior endoscopic procedures.Demographics.ECOG performance status.Laboratory tests: Hematology panel (hemoglobin, platelets, WBC and WBC differential with neutrophils, lymphocytes, monocytes) chemistry panel (sodium, potassium, calcium, creatinine, total and direct bilirubin, alkaline phosphatase, 𝛾GT, ALT, AST, CrP, INR, aPTT, PT) and CA 19 − 9, CEA (optional).

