### Sample size calculation and statistical analysis

The sample size of 120, i.e., 60 patients per group, was calculated based on the two-sided log-rank test for time to first event analysis. Thereby, a power of 80% can be reached under the following assumptions and with a two-sided significance level of 5%. Based on previous reports [7, 9, 14, 20], the event rate at 6 months in the control group was estimated to be 50% and 25% in the intervention group resulting in a hazard ratio (HR) of 0.415. The follow-up will be fixed at 6 months. Furthermore, it was assumed that there will be a low loss to follow-up of 2.5% over six months and all patients stay within their treatment group within the observational period. PASS version 16.0.3 was used for the calculation of the sample size.

Descriptive analysis for baseline characteristics will be performed giving mean, standard deviation, median, and inter-quantile range for continuous data as well as counts and percentages for categorical data. Tests of statistical significance will not be undertaken for baseline characteristics; rather the clinical importance of any imbalance will be noted [22]. A modified ITT (mITT) population will be used for the primary endpoint analysis. The mITT population consists of all patients who will be randomized in the ACTICCA-2 trial and who will undergo endoscopic stenting.

Primary endpoint analysis will be conducted using a cause-specific Cox proportional hazards model comparing the two treatment groups regarding time to first event within 6 months with trial site as random effect (frailty) and tumor location (perihilar vs. ductal) and stent material (plastic vs. metallic) as fixed effects. An adjusted HR for the treatment effect with corresponding 95% CI and p-value will be given as well as cumulative incidences with 95% CIs. The secondary endpoint OS will be analyzed with the Cox proportional hazards model with a frailty for trial site and adjusting for stratification variable tumor location and the variable stent material. Mixed models will be used for further secondary endpoints (linear, logistic, or negative binomial as appropriate).

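### Initial stent versus first stent replacement is known before randomization but is in neither the strata nor the primary model; if it is prognostic, some precision is forgone

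*Protocol article*

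**What the plan says.** Under Patient selection and randomization, Table 1 adds to its limit on earlier stenting that "trial inclusion is possible upon first stent replacement or initial stent placement". The running text of the same section agrees: "first stent replacement or placement of the first stent for tumor-related bile duct obstruction within 3 months prior to study inclusion is allowed". It gives the reason for excluding prior ablation and multiple stenting as "to rule out competing effects on the outcome analysis".

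Allocation is 1:1, "stratified by trial site and tumor location (perihilar vs. ductal"). Under Sample size calculation and statistical analysis, the primary cause-specific Cox model is specified "with trial site as random effect (frailty) and tumor location (perihilar vs. ductal) and stent material (plastic vs. metallic) as fixed effects". The overall survival model uses the same terms. The screening history includes "prior endoscopic procedures", so each patient's position (first stent or first replacement) is on file before allocation.

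That section also says a detailed analysis plan will be finalized before the randomization code is broken. Exploratory subgroup analyses are planned, but their factors are not named.

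**The concern.** A patient at the first replacement has already lived with a stent for this tumor, and a patient at initial placement has not. The two may differ in their risk of the biliary event that the endpoint counts. The protocol itself treats a heavier stenting history as able to affect the outcome. Yet this split is balanced by neither the randomization nor the model, while a factor outside the strata, stent material, is adjusted for.

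If the split is prognostic, two things follow in a trial of 60 per arm. A chance difference in mix shifts the estimated treatment hazard ratio and the specified model cannot correct it. Leaving a prognostic factor out of a Cox model also pulls the hazard ratio somewhat towards 1. Adding the covariate only after an imbalance has been seen would be a data-driven choice in the trial's one confirmatory analysis.

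**Working it through.** **Inputs from the protocol:** 60 per arm; 6-month event rates of 50% (control) and 25% (RFA); hazard ratio 0.415; two-sided 5%; power 80%; 2.5% loss over 6 months; follow-up fixed at 6 months.

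**Assumed, because the documents do not give them:** share of patients entering at first replacement, 30 to 50%; hazard ratio of replacement versus initial stent, 1.5, 2 or 3.

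**1. The plan's own figures.**
- Hazard ratio: ln(0.75)/ln(0.50) = 0.415, as stated.
- Events for 80% power: 41 (Schoenfeld) or 46 (Freedman). The average event rate is (0.50 + 0.25)/2 = 0.375, which gives 41/0.375 = 110 or 46/0.375 = 123 patients before loss.
- A comparison of two proportions needs 58 per arm: 116/0.975 = 119, or 120 when balanced.
- With 120 patients and 2.5% loss, about 44.5 events are expected. Power is then 78.7% (Freedman) or 83.5% (Schoenfeld).

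The stated 120 is therefore reproduced; there is no sample-size error here.

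**2. Chance imbalance.** The 95% range for the difference in share is ±1.96 × √(2p(1 − p)/60):
- p = 0.5: 1.96 × √(0.5/60) = 0.179, or ±18 points
- p = 0.3: 1.96 × √(0.42/60) = 0.164, or ±16 points

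The standard deviation is 8 to 9 points. In simulation the arms differed by 10 points or more in about 25 to 33% of trials.

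**3. Power with the factor omitted or included.** Each scenario has 3000 simulated trials of 120 patients with exponential event times. Control 6-month risk is held at 50% and the treatment hazard ratio within each stent group at 0.415.

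| Factor HR | Share | Omitted | Included | Gain (points) |
|---|---|---|---|---|
| 1.5 | 30% | 80.3% | 81.0% | 0.7 |
| 1.5 | 50% | 80.6% | 81.0% | 0.4 |
| 2 | 30% | 78.3% | 80.0% | 1.7 |
| 2 | 50% | 79.8% | 81.5% | 1.7 |
| 3 | 30% | 76.4% | 81.9% | 5.5 |
| 3 | 50% | 76.8% | 81.0% | 4.2 |

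With no prognostic effect, the two analyses agree to within 0.2 points.

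**4. Same comparison with the planned overall rates (50% and 25%) held, 50% share.** With the factor omitted, power is 80.4% (factor HR 2) or 81.0% (factor HR 3). With it included, power is 82.2% or 85.4%.

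**5. Average estimated treatment hazard ratio when the arms differ by 10 points or more** (same setting as step 3).

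| Factor HR | Omitted, excess of replacements in RFA arm | Omitted, excess in control arm | Included, either direction |
|---|---|---|---|
| 1.5 | 0.43 | 0.39 | 0.40–0.41 |
| 2 | 0.46 | 0.37–0.39 | 0.40–0.415 |
| 3 | 0.49–0.51 | 0.37–0.38 | 0.40–0.41 |

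**6. Under no treatment effect** (50% share; factor HR 1, 2 and 3), the unadjusted analysis rejects in 4.5 to 5.0% of trials.

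The simulations leave out the site frailty, stent material and the competing event of death. They allocate patients without regard to site, so any between-site difference in mix that stratification would balance is not credited.

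**The case against.** Every trial leaves some plausible prognostic factor out of its model, and this one already adjusts for both stratification factors and one more. The protocol set a threshold on prior stenting and placed first replacement on the acceptable side, so its rationale does not concede that this particular split predicts outcome. No figure in the documents shows that it does. An analysis plan that is not shown may also cover it. All of this stands, and it is why the point is an improvement and not an error. The reply is narrow: the protocol does fix the covariates of its confirmatory model, this factor is not among them, and naming it is cheap.

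Three stronger readings are tempting, and the documents do not support them.

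- **That replacement patients have already had a failed stent.** Nothing says so. The trial's own visits at 3 and 6 months include stent replacement as regular management, so a first replacement may be a routine exchange. The Background figure of roughly 30% dysfunction and cholangitis in 3 months makes it plausible that some were failures, but the binary split would mix the two, which could dilute any prognostic effect.
- **That the trial falls short of its 80% power.** The planned 50% and 25% are overall rates. With these held, the analysis without the factor keeps 80.4 to 81.0%. The lower figures in step 3 arise because fixing 0.415 within each stent group makes the overall effect smaller than planned.
- **That the hazard ratio is biased by imbalance.** Chance imbalance has no preferred direction over repeated randomizations, and the type I error stays near 5%.

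**Conclusion.** The factual core holds: a baseline split that the eligibility criteria create, and that is recorded before allocation, is in neither the strata nor the primary model. The consequence is conditional. If the split is prognostic, adjustment steadies the estimate in the trial actually run and adds about 0.5 points of power at a factor hazard ratio of 1.5, about 2 at 2, and 4 to 5.5 at 3. If it is not prognostic, nothing material is lost. These sizes rest on an assumed share of 30 to 50% and assumed factor hazard ratios, since the documents give neither. The stability of the estimate is the stronger argument and power the weaker one.

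**What to change.** Before the randomization code is broken, name the index procedure (initial stent versus first stent replacement) in the analysis plan as a fixed effect in the primary Cox model and the overall survival model. Take it from the screening history and record it as a single eCRF field before allocation. Do not add a stratum, so that the site-by-location strata do not become thinner. If the sponsor prefers to leave the primary model as it is, a named sensitivity analysis with this covariate is the minimum.

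The cost is one field derived from data already collected and one degree of freedom against about 45 expected events (60 × 0.50 + 60 × 0.25 = 45, or about 44.5 after loss). The downside is little or no gain if the split turns out not to be prognostic.
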